## 6.2 Analysis Methods

### Primary outcomes

### Primary analysis

QoR-40 scores at 72 hours post-surgery will be summarised by treatment group using unadjusted means and associated SDs (see Table 10). QoR-40 scores from baseline to 12 months post-randomisation will also be summarised by treatment group using a boxplot.

A mixed effects linear regression model adjusting for type of surgery, baseline QoR-40 scores, age, and gender as fixed effects and recruitment centre as a random effect will be used compare QoR-40 scores at 72 hours post-surgery. The adjusted mean difference between the arms, associated 97.5% confidence interval and associated p-value will be reported (Table 10). The assumption of approximate normality of the residuals will be assessed graphically.

Pain scores from baseline to 12 months post-randomisation will be summarised by treatment group using a boxplot.

A summary statistics approach will be used to calculate the area under the curve (AUC) of cumulative daily pain scores from 6 to 72 hours post-surgery [24]. Specifically, parameters from a repeated measures mixed effects linear regression model will be used to calculate the pain AUC for each treatment group. The model will include repeated measures of the pain scores (level 1) nested within participants (level 2) and adjusted for recruitment centre as a random effect (level 3). Time will be treated as categorical and a treatment by time interaction will be included. The model will be adjusted for type of surgery, baseline pain score, age, gender, and the use of pre-operative opiate pain medication as fixed effects. The AUC for each treatment group and associated SD will be calculated following the formula lay out by Bell et al. [24] and using the lincom command in Stata. Time will be treated linearly and AUCs will be calculated for the median values of continuous covariates and most common value of categorical covariates. These results will be presented as shown in Table 10. Similar methods will be used to calculate the difference between the two groups which will be compared using a t-test. The adjusted difference (97.5% CI) and associated p-value will be presented (Table 10). The assumption of approximate normality of the residuals of the mixed effects model will be assessed graphically.

If, in either case, approximate normality of the residuals is not appropriate, the first approach will be to consider a transformation of the data. If approximate normality cannot be achieved by transformation, the data will be analysed using a non-parametric equivalent with no adjustment. In the case of the AUC analysis, this may result in a return to the summary measures approach (see below). Medians and inter-quartile ranges will be reported for each treatment group.

Note that the above described approach differs from that described in the trial protocol, whereby individual AUCs were calculated separately for each participant, and then analysed using a multivariate regression model, also referred to as summary measures approach. The summary statistics approach described here has been shown to be superior to the summary measures approach in terms of precision, bias and handling of missing observations [24]. The original analysis approach will be performed as a sensitivity analysis as part of the secondary analyses (see below).

These analyses will be conducted for the ITT population as defined in Section 4.2.

**Table 10:** Analysis of co-primary outcomes at primary endpoints (ITT population)

|                              | Intervention |           | Control |           | Adjusted diff | p-value |
|------------------------------|--------------|-----------|---------|-----------|---------------|---------|
|                              | n            | mean (SD) | n       | mean (SD) | (97.5% CI)    |         |
| QoR 40 (72 hours)     | X            | X (X)     | X       | X (X,X)   | X (X)         | X       |
| Pain (AUC 6-72 hours) | X            | X (X)     | X       | X (X,X)   | X (X)         | X       |

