#### 8.4. Baseline Assessments

Prior to randomisation the following information will be collected:

- Patient demographics (gender, age at surgery, body mass index)
- Summary medical history
- Summary medication history (current medication and duration of current medication, changes to current medication in the last 6 months, any history of prior opiate use)
- Quality of Recovery 40
- Pain Visual Analogue Scale (0-10) at rest
- Oxford Knee Score
- Clinical Assessment - American Knee Society Score
- Patient expectations of treatment
- Summary healthcare and social services use as well as informal care in the past 6 months due to knee (GP visits, outpatient visits, allied healthcare contacts, hospital admissions, medications, meals on wheels, and unpaid care)
- Summary employment history (in paid employment, not in employment, time away from work or usual activities)
- EuroQol EQ-5D-5L

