### 3.7 Statistical Analysis Outline

The primary objective of improved patient recovering will be assessed by analysing the two primary endpoints: global QoR-40 scores at 72 hours and cumulative pain score from 6 to 72 hours following surgery. The QoR-40 is a global measure of quality of recovery. It incorporates five dimensions of health: patient support, comfort, emotions, physical independence, and pain; each item is graded on a five-point Likert scale. QoR-40 scores range from 40 (extremely poor quality of recovery) to 200 (excellent quality of recovery) [18]. The null hypothesis that there is no difference between the treatment arms will be rejected if either of these outcomes are statistically different at the 2.5% significance level. The trial will be considered to have a positive result if either of the dual primary outcomes returns a positive result.

Pain scores will be assessed daily in the evening at approximately 6, 24, 48, and 72 hours post-surgery, using a 0-10 VAS and cumulative pain scores will be calculated as area under the curve.

Both of the primary outcomes will be analysed using multivariate linear regression adjusting for stratification factors and other important prognostic variables, including baseline scores in the case of the QoR-40. The adjusted mean difference between the two groups together with 97.5% confidence intervals will be reported for each of the primary outcomes. If either of the primary outcomes is not normally distributed, transformation to normality will be the first approach. If this is not possible, then non-parametric techniques without adjustment will be used.

As secondary analyses both pain and QoR-40 measured at 6, 24, 48 and 72 hours will be assessed using longitudinal methods to take account of the multiple-time points and the correlation between them. Multi-level, multivariate linear regression modelling with adjustment for the same factors as the primary analysis will be used. Other continuous variables will be analysed using similar methodology. For binary variables the number and percentage of patients in each category will be reported for each treatment group and overall. Chi-squared tests will be utilised for comparing the treatments, with additional analyses being undertaken using multi-variate logistic regression with adjustment for stratification and other important prognostic factors if sufficient events have been observed.

Reporting of the results will be based on the CONSORT statement.

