### Secondary analysis

Repeated measures of each of the primary outcomes (at 6, 24, 48, 72 hours, 6 weeks, 6 months and 1 year) will be modelled using multi-level mixed-effects linear regression models. The assumption of approximate normality of the residuals will be assessed graphically. These models will use repeated measures (level 1) nested within participants (level 2) and will include a random effect to account for heterogeneity in response due to recruitment centre (level 3). The models will also include fixed effects for type of surgery (TKR versus UKR), baseline values, age, gender and, in the case of the pain scores, use of pre-operative opiate pain medication. Time will be treated as categorical and interactions between treatment and time will be included in the model to allow for treatment effects to vary over the follow-up. The adjusted difference between treatment groups (and associated 97.5% confidence interval) will be reported (see Table 11). This analysis will be conducted for the ITT population (see Section 4.2).

If, in either case, approximate normality of the residuals is not appropriate, the first approach will be to consider a transformation of the data. If approximate normality cannot be achieved by transformation, the data will be analysed separately at each time point using a non-parametric equivalent with no adjustment. Medians and inter-quartile ranges will be reported for each treatment group.

In addition, a summary measures approach to cumulative pain will also be used as a supporting analysis for this outcome. For each participant, cumulative pain score from 6 to 72 hours post-surgery will be calculated as the area under the curve. Participants with missing pain scores at either 6 or 72 hours will be excluded from this analysis. The potential impact of missing data will be investigated separately. Pain score AUCs will be summarised by treatment group using unadjusted means and associated SDs (Table 11). A multivariate linear regression will be used to compare the AUCs between the treatment groups, adjusted as described previously. The adjusted difference (97.5% CI) and associated p-value will be presented (Table 11).

**Table 11:** Secondary analysis of primary outcomes (ITT population)

|          |                      | Intervention |           | Control |           | Adjusted diff | p-value |
|----------|----------------------|--------------|-----------|---------|-----------|---------------|---------|

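### The co-primary QoR-40 model leaves out pre-operative opiate use, which the co-primary pain model adjusts for, and the SAP gives no reason; the likely cost is a small loss of precision

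*Combined protocol and SAP*

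**What the plan says.** SAP section 6.2 (Primary analysis) sets out two models. The QoR-40 model is a mixed linear regression "adjusting for type of surgery, baseline QoR-40 scores, age, and gender as fixed effects", with recruitment centre random. The pain AUC model, also with centre random, takes "type of surgery, baseline pain score, age, gender, and the use of pre-operative opiate pain medication as fixed effects".

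The secondary longitudinal models in the same section repeat the split. They adjust for type of surgery and for "baseline values, age, gender and, in the case of the pain scores, use of pre-operative opiate pain medication". The covariate sets were therefore chosen separately for each outcome.

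Protocol section 8.4 collects medication history before randomisation, including "any history of prior opiate use". SAP section 3.7 lists the QoR-40 dimensions as "patient support, comfort, emotions, physical independence, and pain". The general rule on adjustment (protocol 11.1, SAP 3.7) is that both primary outcomes are adjusted for the stratification factors and for further prognostic variables, "including baseline scores in the case of the QoR-40". It does not list those further variables.

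**The concern.** By putting pre-operative opiate use in the pain model, the SAP treats it as prognostic for post-operative pain. Two of the five QoR-40 dimensions concern pain and comfort, so some association with the 72-hour QoR-40 is a reasonable expectation. The variable is measured before randomisation, so it is a valid covariate for either outcome. It would use one degree of freedom among about 480 analysed participants.

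At stake is the precision of an outcome that can make the trial positive by itself (SAP 4.1). As written, a chance imbalance in opiate users would be adjusted for in the pain result and left in the QoR-40 result. The planned baseline tables (SAP 5.3, Tables 3 to 5) would not show it, because opiate use is not among their rows.

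**Working it through.** **Inputs from the documents** (protocol 11.2, SAP 3.3): difference 5 points, SD 15.5, two-sided alpha 0.025, power 90%, 240 per arm, 4% loss, 250 per arm randomised. The SD carries no reduction for covariates.

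**Input assumed:** R², the share of the variance remaining after the present covariates that opiate use would explain. The documents give no value, so the range is 0 to 5%.

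**1. The plan's own figure.** n = 2(z₀.₉₈₇₅ + z₀.₉₀)² × SD² / difference² = 2(2.241 + 1.282)² × 15.5² / 5² = 239 per arm by the normal formula, and 240 with the noncentral t. Power at 240 per arm is 90.2%. Inflation gives 240 / 0.96 = 250. The stated figure reproduces, and it relies on no covariate.

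**2. Effect of adding the term at 240 per arm.** Residual SD = 15.5 × √(1 − R²), and SE = residual SD × √(2/240). At R² = 0 the SE is 15.5 × 0.0913 = 1.415, and the 97.5% CI half-width is 2.241 × 1.415 = 3.17. The present model has six fixed coefficients including the intercept, so residual degrees of freedom go from 474 to 473. The net SE ratio is √[(1 − R²) × 474/473]. The centre effect is ignored.

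| Assumed R² | SE | CI half-width | Power | n per arm for 90% | Net SE change, with the lost df |
|---|---|---|---|---|---|
| 0 | 1.415 | 3.17 | 90.2% | 239 | +0.1% |
| 1% | 1.408 | 3.16 | 90.5% | 237 | -0.4% |
| 2% | 1.401 | 3.14 | 90.8% | 234 | -0.9% |
| 3% | 1.394 | 3.12 | 91.1% | 232 | -1.4% |
| 5% | 1.379 | 3.09 | 91.7% | 227 | -2.4% |

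Only the last column includes the lost degree of freedom. Break-even is R² = 1 − 473/474, about 0.2%.

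**3. The same gain in participants.** 480/(1 − R²) − 480 gives about 5, 10 and 15 in the whole trial at R² of 1, 2 and 3%.

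**4. Is the range sensible?** For a binary covariate with prevalence p and an effect of d points given the other covariates, R² ≈ p(1 − p)d²/15.5². With an assumed p = 20%, d = 2 gives 0.3%, d = 5 gives 4/240.25 = 1.7%, and d = 8 gives 4.3%.

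**5. What an imbalance could do.** With the same assumed 20% prevalence, the SE of the difference in proportions is √(2 × 0.2 × 0.8/240) = 3.65 percentage points. A two-SE imbalance of 7.3 points with d = 5 moves the QoR-40 difference by 0.073 × 5 = 0.37 points, about a quarter of the 1.415 SE.

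**6. If the present covariates already help.** Suppose they explain 20% of the total variance. Power is then 95.6% without the opiate term and 96.5% with it at R² = 5%, so the gain is smaller still.

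**The case against.** The split is explicit and consistent across the primary and secondary models, and choosing covariates before unblinding is a judgement the trial team may make. A reader might infer from the general rule on prognostic variables that the SAP breaches the protocol. It does not: neither document lists the variables, mentions opiate use in that rule or requires one set for both outcomes, and the rule itself allows outcome-specific covariates.

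A reader might also infer that precision is certainly being lost. The documents do not show that. They give neither the prevalence of opiate use nor its association with QoR-40. Baseline QoR-40 is already in the model and may absorb much of any association, and three of the five dimensions are not about pain or comfort. Below an R² of about 0.2% there is no gain.

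The change also has a possible cost. SAP 6.3 has rules for missing outcomes and questionnaire items but none for missing baseline covariates. At R² = 1% the gain is worth about 5 participants of 480, so dropping 5 for a missing opiate history would cancel it. Nor do the documents define how the history becomes a model covariate.

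All of this stands as a limit on the claim, but it does not remove the point. The pain model already needs a coding and a rule for missing values, and a simple imputation keeps every participant in the analysis.

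**Conclusion.** The point holds as a minor, optional improvement. The two co-primary models differ in one covariate that is already collected and plausibly prognostic for both outcomes, and the SAP does not say why. The loss of precision is likely but unproven. Over the assumed R² range of 0 to 5%, adding the term changes the SE by +0.1% to -2.4% and lifts power at 240 per arm from 90.2% to at most about 91.7%.

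It would be wrong to read the omission as a bias. Under randomisation the confidence interval already allows for chance imbalance in unadjusted variables, the type I error is unaffected, and the 90% power was calculated without any covariate.

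**What to change.** Before data lock and unblinding, add pre-operative opiate use as a fixed effect to the primary and the secondary longitudinal QoR-40 models. State one yes/no coding from the baseline medication history and use it in both the pain and QoR-40 models. Add a rule for missing baseline covariates, for example mean or missing-indicator imputation, so that no randomised participant is dropped for a missing covariate. The cost is a short SAP amendment and one degree of freedom, with no new data.

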### **8.6.1. Withdrawal from Follow Up**

Participants may withdraw from the follow-up regime. If so, data up to the point of withdrawal will be collated and analysed accordingly.

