### 4.2 Definition of Analysis Populations

Populations for analysis are defined as follows:

Intention to treat (ITT): all participants randomised in their randomised groups.

Per protocol (PP): participants who received the allocated intervention will be analysed according to the treatment they actually received. Participants will be excluded from the PP population if:

- They did not receive the treatment to which they were randomised
- They did not provide sufficient follow-up data for analysis
- They did not satisfy the eligibility criteria for the study

The definition of the PP analysis population will be finalised during a blinded analysis of the data (not separated by treatment group) prior to the final data lock.

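### The deciding QoR-40 analysis uses only the 72-hour score and has no stated method for a missing one, unlike the pain co-primary from the same visits

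*Combined protocol and SAP*

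**What the plan says.** QoR-40 and pain are both collected on the evening of surgery and on days 1, 2 and 3 (protocol 8.5).

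- **QoR-40 primary model (SAP 6.2, Primary analysis).** A linear model with surgery type, baseline QoR-40, age and gender as fixed effects and "recruitment centre as a random effect will be used compare QoR-40 scores at 72 hours post-surgery". No earlier post-operative score enters.
- **Pain primary model (same section).** Here "parameters from a repeated measures mixed effects linear regression model will be used to calculate the pain AUC for each treatment group". The SAP departs from the protocol to do this and gives as its reason that the approach "has been shown to be superior to the summary measures approach in terms of precision, bias and handling of missing observations".
- **Analysis set.** "These analyses will be conducted for the ITT population as defined in Section 4.2", and SAP 4.2 reads "Intention to treat (ITT): all participants randomised in their randomised groups".
- **Missing data.** SAP 6.3 fills in single QoR-40 items when three or fewer are missing and treats the total as missing otherwise. It adds an rctmiss analysis that makes missing QoR-40 outcomes up to 5 points worse than under missing at random. Protocol 11.4 allows multiple imputation where suitable. SAP 6.4 mentions it conditionally and points to 6.3, which contains no imputation model.
- **Secondary model (SAP 6.2, Secondary analysis).** A repeated-measures QoR-40 model from 6 hours to 1 year, in the ITT population, with a 72-hour difference and 97.5% interval in Table 11.
- **Withdrawal (protocol 8.6.1).** "data up to the point of withdrawal will be collated and analysed accordingly".

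**The concern.** As written, the primary QoR-40 model is in effect a complete-case analysis at 72 hours. That is an inference from the model and from the absence of any rule for a missing total, but no other reading is specified.

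Two things follow. The ITT label does not describe the set that produces the estimate. And the two co-primaries, either of which can make the trial positive, treat the same partly observed patient differently, with no reason given.

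Loss at 72 hours could depend on how the patient was doing at 48 hours. Patients who go home early are followed by telephone (protocol 6.3), and fitness for discharge depends partly on pain. SAP 6.3 itself accepts that informative missingness is possible. If such loss differs between arms, the 72-hour comparison is biased, while the scores that would largely correct it are already collected.

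**Working it through.** **1. The plan's own figure.** Inputs from SAP 3.3: difference 5, SD 15.5, two-sided alpha 0.025, power 90%.

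n per arm = 2 × (15.5/5)² × (2.2414 + 1.2816)² = 19.22 × 12.411 = 238.5, so 239. With the t distribution, 240 gives 90.03% power, so the stated 240 is reproduced. 240/0.96 = 250 per arm.

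**2. What loss costs in power.** From 250 per arm, complete-case power is 90.2% at 4% loss and 88.1% at 10%. If the 48-hour score is used, effective n is about 250(1 − d)/(1 − dρ²), where d is the loss and ρ the 48–72 hour correlation. The documents give no ρ; 0.5 to 0.7 is assumed.

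| Loss | n at 72 h | Effective n, ρ = 0.5 to 0.7 | Power |
|---|---|---|---|
| 4% | 240 | 242.4 to 244.8 | 90.5 to 90.8% |
| 10% | 225 | 230.8 to 236.6 | 89.0 to 89.7% |

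At the planned loss the gain is under one percentage point. Power lost through smaller numbers is not the issue.

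**3. Bias.** The sizes were simulated with SD 15.5, loss depending on the 48-hour score with log-odds slope 1 per SD, and a true difference of 5. Correlations, slope and unequal loss rates are assumptions. The 10% level is the plan's allowance for pain, not for QoR-40.

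First, without baseline adjustment, low scorers more likely to be lost:

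| Loss, control v intervention | 72 h only, ρ = 0.5 / 0.7 | Using 48 h |
|---|---|---|
| 4% v 4% | 0.04 / −0.02 | within 0.04 |
| 6% v 2% | −0.27 / −0.37 | within 0.03 |
| 10% v 10% | 0.00 / −0.01 | within 0.02 |
| 15% v 5% | −0.65 / −0.98 | within 0.04 |

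A hand check for 6% v 2%: bias ≈ ρ × SD × m × [d_c/(1 − d_c) − d_i/(1 − d_i)], where m is how far below their arm's mean the lost patients lie at 48 hours, in SDs. With m = 0.9 assumed: 15.5 × 0.9 × (0.0638 − 0.0204) = 0.606; times 0.5 or 0.7 gives 0.30 or 0.42, close to the simulated values.

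The SAP model also adjusts for baseline QoR-40. With an assumed baseline correlation of 0.4 the bias shrinks:

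- loss alike in both arms: about 0;
- 4% average loss (6% v 2%, or score-related in one arm only): about 0.2 to 0.3 points;
- 10% average loss (15% v 5%, or one arm only): about 0.4 to 0.8 points.

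Using the 48-hour score brings all of these to within about 0.1 of zero.

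**4. What that means.** At 4% loss the standard error is 15.5 × √(2/240) = 1.415. A bias of 0.3 against the intervention moves power from 90.2% to Φ(4.7/1.415 − 2.241) = Φ(1.08) = 86%. At 10% loss the standard error is 1.461, and a bias of 0.8 moves power from 88.1% to Φ(4.2/1.461 − 2.241) = Φ(0.63) = 74%. These figures ignore the precision gained from baseline adjustment. The direction depends on which arm loses which patients; the opposite pattern would inflate the difference.

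**The case against.** QoR-40 is defined at a single time point, so a single-time-point regression is a natural, pre-specified choice. The SAP's argument for the pain model compares two ways of computing an AUC, and it makes no claim about single-time-point models. Missing data are not ignored: there is the secondary repeated-measures model, the rctmiss analysis, the imputation clauses, and an extra call for patients who cannot be reached. The 4% allowance already covers the lost numbers. All this stands, and it keeps the point modest. But none of it says how a missing 72-hour total is handled in the estimate that decides the trial, and the missing-data argument applies equally to an endpoint collected at the same visits.

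Stronger readings are tempting but not supported:

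- **That protocol 8.6.1 is breached.** It does not require data before withdrawal to enter the primary model, and the secondary model analyses them.
- **That the bias is large.** Values of 0.4 to 0.7 points at 4% loss and 1.0 to 1.6 at 10%, even after baseline adjustment, arise only if loss rises with recovery in one arm and falls with it in the other. Nothing in the documents suggests this.
- **That rctmiss certainly ignores the earlier scores.** SAP 6.3 does not say what its missing-at-random reference conditions on.

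**Conclusion.** The point holds as a gap and an inconsistency worth correcting. The deciding QoR-40 estimate is in effect complete-case at 72 hours under an ITT label, while the pain co-primary retains patients with partial data. The bias is about zero if loss is alike in both arms. Otherwise it is roughly 4 to 6% of the 5-point target at 4% average loss (0.2/5 to 0.3/5) and 8 to 16% at 10% (0.4/5 to 0.8/5). Only the SD, the target and the loss allowances come from the documents; the size rests on the assumed correlations, slope and unequal loss patterns. The sample size is unaffected.

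**What to change.** In SAP 6.2, define the primary QoR-40 estimate as the 72-hour treatment contrast from a repeated-measures model of the 6, 24, 48 and 72 hour scores. Specify categorical time, a treatment-by-time interaction, the same covariates, centre as a random effect and an unstructured within-patient covariance. Keep the single-time-point model as a sensitivity analysis. Report how many patients contribute with and without a 72-hour score.

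The cost is a SAP amendment. No new data or patients are needed and the estimand stays at 72 hours. The model has to be written out, because the planned secondary model runs to 1 year and states no unstructured covariance. The analysis assumes data are missing at random given the earlier scores. Patients with no post-operative QoR-40 score remain excluded, so the set analysed should be described as such and not simply as all randomised.

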#### 3.3 Sample Size

The trial has been powered for two primary endpoints, QoR-40 at 72 hours and cumulative pain score from 6-72 hours, with adjustment for multiplicity using the Bonferroni method [16]. The trial will be assessed as providing evidence of a difference if either of the two primary endpoints is statistically and clinically significant.

The study requires 240 patients per treatment arm in order to be 90% powered to detect a 5 point difference in global QoR-40 score between groups at a significance level of 0.025 (2-sided, adjusted for multiplicity) assuming the standard deviation is 15.5 [17]. To allow for 4% loss to follow-up this has been inflated to 500 patients (250 per treatment arm).

The study also requires a minimum of 225 patients per treatment arm in order to be 90% powered to detect a standardised difference of 33% between groups in cumulative pain score calculated as area under the curve from 6 to 72 hours post-surgery at a significance level of 0.025 (2-sided, adjusted for multiplicity). Inflating the sample size to 500 patients (250 per treatment arm) will allow for 10% loss to follow up on this variable.

Therefore a total of 500 patients will be randomised (250 per treatment arm).

Checks of the sample size calculations are detailed in the documents PAIN\_SS\_mar2016.rtf and QoR40\_SS\_mar2016 both stored in the confidential statistical section of the TMF.

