## 4. STATISTICAL PRINCIPLES

### 4.1 Statistical Significance and Multiple Testing

A significance level of 0.025 will be used and 97.5% confidence intervals will be presented for each of the two primary outcomes. The trial will be considered to have a positive result if either of the dual primary outcomes returns a positive result at this significance level.

All secondary analyses will be considered as supporting the primary analysis and will be analysed using a significance level of 0.05 with 95% confidence intervals.

Interim analyses of primary and secondary endpoints will not be carried out unless requested by the DSMC. In this case, p-values of 0.001 will be used for significance.

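### Table 10 would print a standard error as the SD of the pain AUC, and the SAP leaves the test and the within-participant covariance for that co-primary outcome open to more than one coding

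*Combined protocol and SAP*

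**What the plan says.** SAP section 6.2 (Primary analysis) fits a mixed model to pain at 6, 24, 48 and 72 hours. It has "repeated measures of the pain scores (level 1) nested within participants (level 2" and centre as a random effect at level 3, with categorical time and a treatment-by-time interaction. Arm summaries come from the fitted coefficients: "The AUC for each treatment group and associated SD will be calculated following the formula" of a cited methods paper, using lincom. The comparison follows: "Similar methods will be used to calculate the difference between the two groups which will be compared using a t-test". An adjusted difference, 97.5% CI and p-value then go into Table 10.

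Table 10 gives both co-primary outcomes a mean and SD per arm. The QoR-40 row is to hold unadjusted means and SDs. SAP section 4.1 sets the standard: "A significance level of 0.025 will be used and 97.5% confidence intervals will be presented for each of the two primary outcomes".

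The SAP states no variance source or degrees of freedom for the t-test, and no participant-level or residual covariance. The models running out to 1 year repeat the nesting phrase: "These models will use repeated measures (level 1) nested within participants (level 2". The same part of section 6.2 also plans a per-participant AUC, summarised in Table 11 with unadjusted means and SDs.

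**The concern.** Three things in one paragraph bear on a primary result.

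- **The SD.** A linear combination of model coefficients carries a standard error. Printed as an SD, it misstates between-patient spread, and the error is hard to see because the row above holds real SDs. Anyone forming a standardised effect from Table 10, for instance to compare it with the design target, would be badly misled.
- **The test.** The preceding sentences produce two arm means with things called SDs, which are the usual inputs to a two-sample t-test. An analyst could take the sentence that way.
- **The covariance.** Nesting levels alone are commonly coded as a random intercept, which forces equal variances and equal correlations at the four times. If pain does not behave like that, the standard error of the AUC difference is off.

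**Working it through.** **The plan's own figure.** SAP section 3.3: "The study also requires a minimum of 225 patients per treatment arm in order to be 90% powered to detect a standardised difference of 33" per cent. n = 2(z₀.₉₈₇₅ + z₀.₉₀)²/d² = 2(2.2414 + 1.2816)²/d², which gives 223.4 (224) for d = 1/3 and 227.9 (228) for d = 0.33. The noncentral-t versions give 225 and 230. 225/0.9 = 250. The sample size reproduces and is not in question.

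**AUC weights.** The trapezoid rule gives (24−6)/2 = 9, (48−6)/2 = 21, (72−24)/2 = 24 and (72−48)/2 = 12 hours, total 66. With w = (9, 21, 24, 12) and S the covariance of the four scores, the SD of an individual AUC is √(w′Sw). With no centre effect, the SE of an arm's AUC is √(w′Sw/n).

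**SE printed as SD.** The ratio of SD to SE is √n: √225 = 15.0, √250 = 15.8. No assumption about pain spread is needed. If centre variance enters the arm SE (assumptions: 10 centres, centre ICC 0.03), the SE in SD units is √(0.03/10 + 0.97/n), so the ratio is 11.7 at n = 225 and 12.1 at n = 250. An ICC of 0.05 would give about 10.5. Covariate adjustment is left out. For scale, with an assumed VAS SD of 2.5 and correlation of 0.5, the AUC SD is 132.3 and the SE 132.3/15 = 8.8 point-hours.

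**The test, by reading.**
- *Contrast over its own SE:* valid. t against z matters little: 2.249 (448 df) against 2.241, a 0.3% wider interval.
- *lincom SEs entered as SDs with n (no centre effect):* the statistic is √n times too large. At n = 240 the false-positive rate is 2(1 − Φ(2.2414/√240)) = 88%.
- *Arm SEs combined as independent (240 per arm, assumed AUC SD 130):* shared centre uncertainty is counted although it cancels in the difference. At ICC 0.03, the arm SE is √(0.03×130²/10 + 0.97×130²/240) = 10.91, and √2 × 10.91 = 15.43 against a true 130√(2×0.97/240) = 11.69, 32% too large. Power for 0.33 SD (42.9 point-hours) falls from Φ(42.9/11.69 − 2.2414) = 92% to Φ((42.9 − 2.2414×15.43)/11.69) = 76%. The SE excess is 0% at ICC 0, 11% at 0.01 and 50% at 0.05.

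**Random intercept only.** With complete data, the model replaces S by a compound-symmetry matrix C holding its average variance v and average covariance c. The SE ratio is r = √(w′Cw/w′Sw), and actual alpha is 2(1 − Φ(2.2414 r)). Here w′Cw = (v − c)Σw² + c(Σw)², with Σw² = 1242 and (Σw)² = 4356. Example, SD 2.5 throughout and AR(1) correlation 0.5: v = 6.25, c = 2.2135, w′Cw = 14,655, w′Sw = 15,525, r = 0.972, alpha 0.029.

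The documents give no VAS SDs or correlations, so every pattern is an assumption:

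| SDs at 6, 24, 48, 72 h | Correlation | SE ratio | Actual alpha |
|---|---|---|---|
| any, equal | equal | 1.00 | 0.025 |
| 2.5 throughout | AR(1) 0.4–0.8 | 0.97–0.99 | 0.030–0.027 |
| 2.0, 2.6, 2.6, 2.2 | AR(1) 0.4–0.8 | 0.93–0.95 | 0.038–0.034 |
| 1.8, 2.5, 2.7, 2.7 | AR(1) 0.4–0.8 | 0.93–0.95 | 0.037–0.033 |
| 3.0, 2.5, 2.0, 2.0 | AR(1) 0.4–0.8 | 1.02 | 0.023–0.022 |
| 2, 3, 3, 2 | AR(1) 0.5 | 0.90 | 0.044 |
| 3, 2, 2, 3 | equal, 0.5 | 1.09 | 0.014 |

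**The case against.** The strongest reply is that the primary test is sound as intended. The difference is to be obtained by methods similar to those for the arms, that is by lincom, and it is reported as an adjusted difference with a 97.5% CI. A t-test of that contrast against its own standard error is valid and does not use the mislabelled arm value. This stands. A reader might infer from the t-test sentence that the primary p-value is wrong, with 88% false positives or a large loss of power. Those figures belong only to codings that the SAP does not state, and the second also needs an assumed centre ICC.

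A reader might likewise infer that the SAP has chosen a random-intercept model. It has not: it gives levels and leaves the structure unstated. That is a gap, not a demonstrated error, and its effect could run either way.

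Two safeguards exist. Table 11 will carry raw AUC SDs, and SAP section 7 has an independent statistician repeat the co-primary analyses. Both reduce the risk. Neither corrects the Table 10 label, and someone replicating from this text needs the contrast defined.

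The cited formula was not available, so whether it yields a between-patient SD by another route cannot be checked. lincom itself does not.

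**Conclusion.** The Table 10 label is wrong as written if the value comes from lincom: the printed SD would be roughly 12 to 16 times too small at 225 to 250 per arm. The upper end is √n with no centre effect. The lower end assumes 10 centres and a centre ICC of 0.03.

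The primary test is ambiguous rather than wrong. Its natural reading is valid, but the wording also admits an invalid one.

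The covariance is unspecified. A random intercept alone would put actual alpha at about 2.2% to 3.8% against 2.5% for assumed SDs of 1.8 to 3 with AR(1) correlations of 0.4 to 0.8. More extreme patterns give 1.4% to 4.4%. These figures are analytic, for complete data and without covariates. The effect is modest and its direction unknown. No error is shown in the seven-time-point secondary models.

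**What to change.** Three edits to SAP section 6.2, with no new data:

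1. In Table 10, report the arm AUCs with a labelled SE or 97.5% CI. Leave raw SDs to the per-participant AUC already planned for Table 11.
2. Replace the t-test sentence. Define the AUC difference, its 97.5% CI and its p-value as one linear combination: weights 9, 21, 24 and 12 hours on the treatment differences at 6, 24, 48 and 72 hours. With 6 hours as the reference time, that is 66 × treatment + 21 × (treatment by 24 h) + 24 × (treatment by 48 h) + 12 × (treatment by 72 h).
3. Specify an unstructured within-participant residual covariance for the four-time-point primary model.

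The cost is a few more covariance parameters, ten variances and covariances for four times, which about 480 patients can support. The degrees-of-freedom method is immaterial at this size.
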